	**Interventional allergens**			
	**Peanut**	**Hazelnut**	**Hen’s egg**	**Cow’s milk**
**Amount of protein [mg/3 g] to be taken once daily**	1.7	1.9	1.8	2.0

The sugar-free, rusk-like biscuit powder (3 g of powder/day using a measuring spoon) will be mixed with water, and optionally fruits, to a puree. The study product should be eaten daily throughout the study duration. The first feeding of the study product at visit 1 (V1) will be performed under medical supervision at the study center. The duration of the intervention is determined by the date of the routinely scheduled OFC at visit 2 (V2) and should be at least 3 months and up to 6 months after inclusion to the trial. In case of a postponed OFC (e.g., due to illness of the child), the duration of the intervention can be extended up to a maximum of 9 months.

In the placebo group, subjects consume daily the same sugar-free rusk-like biscuit powder, however, without cow’s milk, hen’s egg, peanuts, or hazelnuts following the same instructions as the active group. To ensure blinding, the first feeding of the placebo study product will also be performed under medical supervision at the study site.

In infants, first, weaning foods (e.g., vegetables) should have been successfully introduced for at least 1 week before feeding the study product. Mothers will be encouraged to continue breastfeeding while introducing weaning foods. Parents of both groups will be advised to avoid cow’s milk, hen’s egg, peanuts, hazelnuts, or their products in their child’s diet according to the individual sensitization profile.

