#### Strategies to improve adherence to interventions {11c}

The parents of the study participants will be asked to maintain a weekly (e-)diary from V1 onwards to document consumption and any adverse events. In case of e-diaries, data are stored directly in a central database REDCap. Furthermore, patients will be called once during the study (phone call (PC)) to investigate compliance and tolerability of the regimen. They will be instructed to contact the investigation site by phone in the case of any objective immediate-type allergic reaction occurring within 2 h after food consumption including accidental allergic reactions to other food allergens. Also at V2, compliance, tolerability, and the entries of the (e-)diary will be reviewed and discussed with the investigator or delegated study staff.

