#### Participant timeline {13}

During the screening visit (V1), the participation criteria will be checked, and information on demographics, subject/family characteristics, relevant medical history, medication, and nutrition will be recorded. In addition, anthropometric measurements and a physical examination will be performed including the assessment of the severity of eczema (in case of eczema). Skin swabs and stool and saliva samples will be collected. Blood will be collected, or a skin prick test (SPT) will be performed, if the child’s sensitization status was assessed ≥ 3 months prior to V1. Transepidermal water loss (TEWL) will be measured, and palmar hyperlinearity will be determined. Parents are asked to collect a dust sample from the bed and living room within 24 h prior to both study visits. Eligible children will be randomized to one of the two study groups. The first feeding of the study product will be performed at the study site. The study product will be dispensed. Parents will be asked to fill out a (e-)diary for the entire study period (from V1 to V2). Two weeks after V1, parents will be called (PC1) to review compliance, tolerance of the study product, and adverse events. The study product will be consumed daily until an oral food challenge in routine diagnostics at V2 will be performed after their individual waiting time of 3–6 months. At V2, information on medical history, medication, and nutrition will be recorded. In addition, anthropometric measurements and a physical examination will be performed. Skin swabs and stool and saliva samples will be collected. TEWL will be measured. A blood sample will be collected, and a SPT with cow’s milk, hen’s egg, peanuts, and hazelnuts will be performed. Oral food challenges will be performed according to standardized procedures in a double-blinded placebo-controlled manner (Table 3).

**Table 3 Tab3:** Study visits and procedures

	**Visit 1 (V1)**	**Phone call 1 (PC1)**	**Visit 2 (V2)**
Time	0 weeks, baseline	2 weeks (± 5 days) after V1	3–6 months after V1 ± 14 days
Informed consent	x		
Check eligibility	x		
Randomization	x		
Demographics/subject characteristics	x		x
Family characteristics	x		x
Medical history	x		x
Review adverse events (AEs)		x	x
Review concomitant medication	x	x	x
Nutritional characteristics	x		x
Physical examination	x		x
SCORAD, EASIscore (in case of eczema)	x		x
Transepidermal water loss measurement (TEWL)	x		x
Palmar hyperlinearity	X		
Skin prick testing	(x)^a^		x

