
#### Plans to promote participant retention and complete follow-up {18b}

Two weeks after V1, parents will be called (PC1) to investigate compliance and tolerability of the study product. In case of discontinuation of the intervention or deviation from the study protocol, participants are encouraged to maintain the scheduled visits or phone calls, and collection of all possible data is planned.

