## Statistical methods

### Statistical methods for primary and secondary outcomes {20a}

The primary analysis of the primary endpoint will be performed by logistic regression with (fixed) factor treatment group (verum, placebo regarding the primary allergen) and the stratification factors primary allergen (hen’s egg, cow’s milk, peanuts, hazelnuts), age group (≤ 2, > 2 years of age), grade of sensitization (low, medium, and high), and planned duration of intervention (< 5, ≥ 5 months). In case of stratification groups with very few cases, stratification groups may be combined (e.g., low vs. medium/high grade of sensitization) or the factor omitted from the analysis model; the decision will be finalized, blinded, and described in the statistical analysis plan (SAP). From this model, the odds ratio for verum vs. placebo treatment will be calculated with a 95% confidence interval and a *p*-value for the treatment group comparison. The analysis will be performed on the full analysis set (FAS) based on the intention-to-treat principle without imputation of missing values. The significance level will be set to 0.05 (two-sided). All other analyses will be considered explorative. Several explorative sensitivity analyses will be performed for the primary endpoint: a re-run of the primary analysis model with the per-protocol population (instead of the FAS). In case of relevant differences between the treatment groups with respect to baseline variables, the primary analysis will be repeated with further adjustment variables (FAS population). To account for the potentially varying lengths of follow-up, a Cox proportional hazards regression as well as Poisson regression will be used to analyze the primary endpoint. Explorative analysis of secondary endpoints will follow the same principle as the primary analysis of the primary endpoint, i.e., models with the (fixed) factor treatment group and the stratification factors. Binary endpoints will be analyzed by logistic regression; continuous endpoints will be analyzed by analysis of covariance (ANCOVA) with the respective baseline value (if available) as an additional covariate. Secondary endpoints will be analyzed with the FAS. Regarding safety endpoints, the nature, frequency, and severity of adverse events and safety variables, including serious adverse events, will be summarized descriptively by treatment group (based on the safety population of all participants who received at least one dose of study treatment and have at least one post-baseline safety assessment, analyzed according to the treatment received). Further details will be described in the SAP, which will be finalized prior to data analysis.

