Any serious allergic reaction related to the study intervention will lead to a temporary halt of the study in order to re-evaluate the safety conditions. For this purpose, an external safety advisory board is called in to advise the PI and the CO-PI of the study. Based on the recommendations of this committee, a decision is made as to whether the study can be continued or whether changes to the design need to be made. If three participants experience serious allergic reactions related to the study intervention, the study will be stopped.

AE/AEI recording will extend from enrollment until the end of the study at V2.

Parents of the participants should document all AEs and AEIs occurring during the study in the subject’s (e-)diary. Moreover, the subject’s parents will be instructed to document accidental food allergen exposures in detail in the (e-)diary and to contact the study site after any known or suspected food allergen exposure, even if it does not cause symptoms. In case of an immediate type allergic reaction after food exposure (either to the study product or due to exposure to (other) food allergens) or recurrent GI symptoms, parents of the participants are asked to call the study site. During the phone call and the second study visit, the subject’s parents/caregivers will be queried on AEs/AEIs based on the patient’s diary and changes in the subject’s condition.

For this specific protocol, only AEIs (see above) and SAEs are logged as (S)AEs in the eCRF. Information will be recorded regarding the date of onset, date of resolution, seriousness, severity, outcome, treatment required, causality, action taken with the study intervention if applicable, possible augmentation factors, and/or other possible causes. For scoring the severity of immediate-type allergic reactions, the grading system for food-induced anaphylaxis published by Sampson is used [14].

The investigators will assess the causality/relationship between the study intervention and the AE. Causality will be documented as related or not related to the intake of the study intervention. Overall, the occurrence of immediate type allergic reactions within 2–3 h after food allergen exposure (study intervention and/or accidental exposure) will be considered as related to food exposure.

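### Because the safety population requires a post-baseline assessment, a child who reacts to the first dose at V1 and withdraws before the two-week call could drop out of the safety tables

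*Protocol article*

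**What the plan says.** All references are to the protocol article.

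- **Analysis set.** Statistical methods {20a} bases the descriptive safety summary on "all participants who received at least one dose of study treatment and have at least one post-baseline safety assessment", grouped by the treatment actually received. The article does not say what counts as a post-baseline safety assessment.
- **First dose.** Intervention description {11a}: "The first feeding of the study product at visit 1 (V1) will be performed under medical supervision at the study center". The same applies to placebo, to protect blinding.
- **Visit labels and schedule.** Table 3 in Participant timeline {13} gives the time of V1 as "0 weeks, baseline". The row that begins "Review adverse events (AEs" is ticked at PC1 and V2 and not at V1. The row for tolerance of the study product is ticked in the same way.
- **First scheduled contact after V1.** Participant timeline {13}: "Two weeks after V1, parents will be called (PC1) to review compliance, tolerance of the study product, and adverse events".
- **Recording of events.** Adverse event reporting {22}: "AE/AEI recording will extend from enrollment until the end of the study at V2". Under Strategies to improve adherence {11c}, parents are asked to "maintain a weekly (e-)diary from V1 onwards to document consumption and any adverse events".
- **After discontinuation.** Under Participant retention {18b}, "participants are encouraged to maintain the scheduled visits or phone calls, and collection of all possible data is planned".

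**The concern.** The second condition makes membership of the safety set depend on something that happens after dosing. By the labels and ticks in Table 3, the first scheduled safety review after baseline is PC1, two weeks after the first exposure. A reaction at V1 is a plausible reason for a family to leave before then, so the condition can remove a child because of the event that the table is meant to count.

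The effect would not be balanced between the groups. The placebo powder contains none of the four target allergens, so a true target-allergen reaction to the product can arise only in the active group. Any such exclusion would lower the active group's reported reaction rate.

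Safety matters here because it is part of the trial's aim and a stated secondary objective. The children have never eaten the food in relevant amounts, and some will have high specific IgE, so the first exposure is especially informative. No data monitoring committee is planned, so the final safety tables carry much of the reported evidence on harm.

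**Working it through.** **Step 1: group size.** The plan's own figure reproduces. For 35% vs 60%, two-sided 5% and 80% power, the chi-squared formula with pooled variance and no continuity correction gives 62 per group (power 80.4%). Allowing for 10% dropout, 124 / (1 − 0.10) = 137.8, so 138 in total and 69 per group. The point does not depend on this calculation. It only supplies the 69, and I assume that all 69 active children are dosed.

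**Step 2: which children meet the second condition?** There are two readings.

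- *Observation after the V1 feeding counts as post-baseline.* Then every child fed under supervision qualifies, and the condition does almost nothing.
- *V1 is baseline, as Table 3 labels it.* Then a child with data from V1 only does not qualify. This child has been dosed and may have had a reaction seen by staff, but is outside the set.

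So the condition is either redundant or potentially harmful. In neither case does it help the safety summary.

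**Step 3: how many first-dose reactors might there be?** The article gives no first-dose reaction rate, so this step rests on assumptions.

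- The Discussion says that the doses reflect the ED05, at which 5% of the allergic population is predicted to react. I assume that this 5% applies to the first dose of one food.
- The proportion allergic at V1 is not given. I use 35% and 60% (the planning rates for the primary endpoint after the intervention, not baseline rates) and 100% as the upper limit.

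With p = 0.05 × proportion allergic, the expected number is 69 × p and the chance of at least one is 1 − (1 − p)^69.

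| Proportion allergic | p | Expected reactors | Chance of at least one |
|---|---|---|---|
| 35% | 0.0175 | 1.2 | 70% |
| 60% | 0.03 | 2.1 | 88% |
| 100% | 0.05 | 3.5 | 97% |

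**Step 4: what would losing one reactor do?** An excluded child leaves both numerator and denominator.

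- Two reactors: 2/69 = 2.9% becomes 1/68 = 1.5%.
- Three reactors: 3/69 = 4.3% becomes 2/68 = 2.9%.

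**Step 5: what cannot be computed.** The article gives no withdrawal rate between V1 and PC1, and none among children who react. The only related figure is about 10% dropout over the whole trial. The expected number of excluded reactors is therefore unknown and may be zero.

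**The case against.** A reader might infer that the plan does remove these children, or that their reactions disappear from the trial. The article supports neither.

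- **The exclusion is one reading of an undefined term.** No section equates a post-baseline safety assessment with the ticks in Table 3. The feeding is supervised, event recording runs from enrollment, the diary starts at V1, and parents are asked to phone after an immediate-type reaction. The statistical analysis plan, which is not shown, may settle the term. This stands: the most that can be said is that such a child could be excluded. Recording an event does not in itself place the child in the analysis set, however, so the wording still needs correction.
- **The scenario is narrow.** Stopping the product is not withdrawal. Participants are encouraged to stay in follow-up, a single product can be stopped while others continue, and the children already have a challenge scheduled at the same hospital. This also stands. It makes the loss less likely without ruling it out, since families may leave completely.
- **The reaction is counted elsewhere.** The frequency and severity of immediate-type allergic symptoms is a secondary endpoint analysed in the full analysis set, which the disputed condition does not govern. Serious related reactions also trigger the halt and stopping rules in {22}, whatever the analysis set. The concern is therefore confined to the descriptive safety tables. The safeguard is partial: secondary endpoints are assessed at V2 and missing values are not imputed, so a child who left before PC1 may have no value there.

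**Conclusion.** The point holds as a weakness in a stated rule. The second condition allows a dosed child who reacts at V1 and withdraws completely before PC1 to be left out of the descriptive safety tables, for a reason tied to the outcome and, for true target-allergen reactions to the product, only in the active group. It does not establish that any child will be excluded.

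The possible size is small in count but large relative to the expected events. Under the ED05 assumption, about 1.2 to 3.5 first-dose reactors are expected among 69 active children, so losing even one would visibly change the reported rate. The number who would withdraw before PC1 is unknown. The primary analysis, power and sample size are not affected.

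**What to change.** - In Statistical methods {20a}, define the safety population as all participants who received at least one dose of study product, analysed by treatment received. This only requires deleting the condition on a post-baseline assessment.
- In Table 3, tick adverse event review at V1, after the first feeding, so that the schedule agrees with the recording period in {22}.

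The cost is one deleted clause and one added tick, carried through to the statistical analysis plan. Reported reaction rates may be slightly higher, and a few children with very little follow-up will enter the denominator. Reporting the length of follow-up beside the safety tables would make the second effect visible.

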
### Interim analyses {21b}

No interim analyses for efficacy are planned.

### Methods for additional analyses (e.g., subgroup analyses) {20b}

Several exploratory subgroup analysis will be conducted regarding the following subgroups: age groups (≤ 2 vs. > 2 years of age); grade of sensitization of the primary food allergen (low vs. medium vs. high); sIgE levels of the primary food allergen according to CAP classes, which are classified into low, medium, and high categories (low: IgE ≥ 0.10 ≤ 3.50: CAP 0–2 vs. medium: IgE > 3.50 ≤ 50.0: CAP 3–4 vs. high: IgE > 50.0: CAP 5–6); sensitization levels of the primary food allergen according to skin prick test results, classified into low, medium, and high (low: wheal size ≥ 3 mm ≤ 5 mm, medium: wheal size > 5 mm ≤ 9 mm, and high: wheal size > 9 mm); duration of intervention (< 5 vs. ≥ 5 months); primary allergen (hen’s egg, cow’s milk, peanuts, hazelnuts); children with eczema (yes/no); carrier of mutations in the filaggrin gene (yes/no): infants with at least one parent with eczema (yes/no); and infants with at least one parent with atopic diseases (asthma, allergic rhinoconjunctivitis, and/or eczema) (yes/no). Subgroup analyses will be performed by additionally including the subgroup variable and the interaction term (subgroup × treatment group) into the primary analysis model (FAS population).

### Methods in analysis to handle protocol non-adherence and any statistical methods to handle missing data {20c}

Selected secondary endpoints will also be analyzed with the per-protocol (PP) population. The PP is a subset of the FAS defined without participants with repeated insufficient consumption of the study product (verum), i.e., consumption < 3 times/week for 3 weeks (either during 3 consecutive weeks or three repeated events of 1 week); OFC taking place before 3 months (after starting the intervention); or OFC taking place after more than 9 months (after starting the intervention). As a general strategy, missing data will not be imputed in this study.

### Plans to give access to the full protocol, participant-level data, and statistical code {31c}

Data will be available upon reasonable request with restrictions regarding scientific purpose and data protection.

### Oversight and monitoring

#### Composition of the coordinating center and trial steering committee {5d}

Trial Management Committee members are KB, MW, BK, and [name]. The steering committee of the CRU will advise on the performance of the project throughout the duration of the trial. Clinical trial monitoring is carried out by the Clinical Trial Office of the Clinical Study Center of the Charité – Universitätsmedizin Berlin and Berlin Institute of Health (BIH). Monitoring will be carried out according to the monitoring manual and depends on the enrollment rate and the data quality. Moreover, there is an external scientific advisory board (SAB), whose members are experts in the field of food allergy, including a representative from the patient organization DAAB (German Allergy and Asthma Association) in order to address particular aspects from the patient side.

#### Composition of the data monitoring committee, its role, and reporting structure {21a}

As the overall risk to patients is low, a data monitoring committee will not be conducted.

#### Adverse event reporting and harms {22}

Pre-existing diseases will be recorded in the subject’s file and in the eCRF system under medical and/or allergy history. Subject reported or physician confirmed worsening of these conditions, or a change of prescribed medication will be assessed during the study visit/phone call and documented in the subject’s file/source data. However, worsening of pre-existing diseases will not be considered as AEs, except those categorized as AEs of special interest (AEIs).

For this specific protocol, AEIs include immediate-type allergic reaction after food exposure, worsening of eczema (in case of eczema), and defined gastrointestinal (GI) symptoms (abdominal pain, bloating, vomiting, difficulties swallowing, stool irregularities).

An accidental food allergen exposure is any known or suspected exposure to a food to which the subject is allergic or sensitized without known clinical relevance, whether or not it results in an AEI.

A serious adverse event (SAE) or serious adverse reaction is defined as any untoward medical occurrence that leads to death, is life-threatening, requires inpatient hospitalization (longer than 24 h), or prolongs an existing hospitalization or results in persistent or significant disability or incapacity. Excluded from this definition are hospitalizations as treatments of a pre-existing condition planned before inclusion into the study or elective surgeries, planned before inclusion into or during the study. According to the seriousness grading, the investigators will review each AE. If the criteria for a SAE are met, the clinical research site will follow local procedures according to the GCP guidelines. All expected and unexpected serious adverse events occurring after the subject’s parents/caregivers have signed the informed consent and the intervention has been started must be reported on a SAE form to the study principal investigator within 24 h of becoming aware of the event.

Any serious allergic reaction related to the study intervention will lead to a temporary halt of the study in order to re-evaluate the safety conditions. For this purpose, an external safety advisory board is called in to advise the PI and the CO-PI of the study. Based on the recommendations of this committee, a decision is made as to whether the study can be continued or whether changes to the design need to be made. If three participants experience serious allergic reactions related to the study intervention, the study will be stopped.

AE/AEI recording will extend from enrollment until the end of the study at V2.

Parents of the participants should document all AEs and AEIs occurring during the study in the subject’s (e-)diary. Moreover, the subject’s parents will be instructed to document accidental food allergen exposures in detail in the (e-)diary and to contact the study site after any known or suspected food allergen exposure, even if it does not cause symptoms. In case of an immediate type allergic reaction after food exposure (either to the study product or due to exposure to (other) food allergens) or recurrent GI symptoms, parents of the participants are asked to call the study site. During the phone call and the second study visit, the subject’s parents/caregivers will be queried on AEs/AEIs based on the patient’s diary and changes in the subject’s condition.

For this specific protocol, only AEIs (see above) and SAEs are logged as (S)AEs in the eCRF. Information will be recorded regarding the date of onset, date of resolution, seriousness, severity, outcome, treatment required, causality, action taken with the study intervention if applicable, possible augmentation factors, and/or other possible causes. For scoring the severity of immediate-type allergic reactions, the grading system for food-induced anaphylaxis published by Sampson is used [14].

The investigators will assess the causality/relationship between the study intervention and the AE. Causality will be documented as related or not related to the intake of the study intervention. Overall, the occurrence of immediate type allergic reactions within 2–3 h after food allergen exposure (study intervention and/or accidental exposure) will be considered as related to food exposure.

